**3. Description of the project**

**3.1. Rationale and objectives of the study**

**3.1.1. Rationale**

Uterine leiomyomata are common pelvic tumors occurring in up to 20% of women over 30 years of age, and represent one of the most frequent indications for operative procedures in women of reproductive age. (Buttram et al 1981) The growth of the fibroids seems to be dependent of ovarian steroids and receptors for both estrogen and progesterone have been identified in fibroids (Wilson et al 1980, Soules et al 1982).

That progesterone may play a role in leiomyomata growth is further supported by the finding of a higher mitotic count in leiomyomata obtained during the secretory phase than in the proliferative phase of the menstrual cycle. (Kawaguchi et al 1989)

The antiprogesteron mifepristone is a synthetic steroid hormone that binds with high affinity to the progesterone receptor thereby preventing the effect of progesterone. Administration of mifepristone has various effects on reproductive function, depending on the dose and stage of the menstrual cycle. When administered in the follicular phase of the cycle, mifepristone inhibits the process of follicular maturation and blocks ovulation.

Previous studies have shown positive effects after treatment with mifepristone when administered 25-50 mg daily for 3 months. All women became amenorrhoeic during treatment and the size of the fibroids decreased with approximately 50% (Kettel et al 1994). Studies using even higher doses of mifepristone for longer periods than 3 months have not revealed any significant risk of endometrial hyperplasia (Murphy et al 1995).

Ovarian steroids also have an effect on breast tissue. Concern has been raised about hormone replace treatment (HRT) with estrogen and progesterone. Various antiprogestins have been proposed as effective for inhibiting tissue growth in the breast. It would therefore be of importance to evaluate the effect of antiprogestins on the breast tissue.

Apoptosis (programmed cell-death) and cell proliferation seem to be closely linked according to experimental evidence. Many proteins that can induce cell death are also components of the cell cycle (Meikrantz et al 1995, Huang et al 1997). The balance between cell proliferation and cell death determines tumor growth in the endometrium as well as in the breast tissue. Specific markers for proliferation (Ki-67) and apoptosis (proteins from the Bcl-2- family) have been identified.

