**3.1.2. Objectives**

The objectives of the present study are

1. To develop a new non-surgical method for treatment of uterine fibroids
2. To study the effect of mifepristone on the size of uterine fibroids
3. To evaluate factors regulating fibroid growth by comparison with untreated fibroids and normal myometrium
4. To study the effect of mifepristone on the amount of blood loss and pelvic pain in patients with fibroids
5. To study the effect of mifepristone on proliferation of breast tissue
6. To study the effect of mifepristone on body composition and cortisol levels

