**3.3. Design and methodology**

**3.3.1. General outline**

This is a pilot study to evaluate the effect of mifepristone on uterine fibroids. The study will include 40 women with uterine fibroids, recruited from the waiting list for hysterectomy. After inclusion women will be randomized to treatment with mifepristone or a placebo (i.e B-vitamin tablets). An ultrasound examination will be performed at start and repeated every 4th week. The total volume of the uterus will be measured as well as each fibroid, and also a Doppler examination of the blood vessels to the fibroids. An biopsy from the fibroid will be obtained at the same time. Endomtrial biopsies will be obtained prior to study start and at surgery for safety reasons and will undergo histological analyses.

Blood will be drawn for analyses of liver function and hemoglobin values as well as estradiol, progesterone, LH, FSH, SHBG, androstendione and DHEAS once a month. A 24 hour urine collection for cortisol levels will be performed and a measurement of body composition with bioelectrical impedance analysis (BIA). This will give information about body cell mass, fat-free mass and total body water. These tests will be repeated after the treatment period.

Women that have not had a mammography during the last 12 months will be offered to have one before the start of the study. A fine-needle-aspiration, from one breast will be performed before, and after the treatment period, for cytological analyses of apoptotic and proliferative factors i.e. Bcl-2, Ki-67 and receptors for estrogen and progesteron. Fine needle aspirations will be performed at the Dept of Cytology, KS in collaboration with [name].

The women will be given Mifegyne 200 mg tablets or B-vitamins and instructed to divide the tablets into 4 parts. One quarter of the vitamin or Mifegyne tablet (50 mg mifepristone), will be taken orally every other day for 3 months. A diary card will be handed out for self registration of bleeding (days and amount), pelvic pain and any side effects.

After the treatment period the woman will undergo surgery as planned. After the uterus has been removed it will be weighed and biopsies from the myomas will be taken for analysis of apoptotic and proliferative factors i.e. Bcl-2, Ki-67 and steroid receptors. Finally the uterus will be examined by a pathologist as part of the usual routine procedure.

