## Statistics

*Sample size calculation*Assuming a standard deviation of 10% in the percentage volume change, 18
 subjects per group will be required to detect a difference of at least 10%
 in the percentage volume change between the treated and the placebo groups
 with 90% power, using a one-sided 5% level test. Allowing for a 10%
 drop outs, 20 subjects per group, or a total of 40, will be recruited into
 the trial.

*Analysis*

 Myoma volume: Repeated measures analysis techniques will be used. For each group, the
 change at each time point will be compared with the baseline value and the
 percentage change with respect to baseline will be estimated. A repeated
 measures model with the baseline volume as a covariate will be used to
 compare the volume at different times between the two groups. Changes will
 be plotted on the absolute scale and will also be expressed as percentage
 change with respect to baseline.

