# Bleeding pattern, BIA and laboratory analysis will be compared using the students-t-test.

For evaluation of immunohistochemistry and molecular biology assays of uterine and breast tissue the paired and unpaired Wilcoxon´s tests will be used as appropriate.

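### Laboratory values are to be compared by an unqualified Student's t-test, with no stated use of the monthly repeats or the pre-treatment value, although the myoma-volume analysis uses both

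*Protocol*

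**What the plan says.** The Statistics part of the Protocol (under 3.3.8-10) gives one sentence to these outcomes: "Bleeding pattern, BIA and laboratory analysis will be compared using the students-t-test". It names no scale, time point, per-woman summary or use of baseline.

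Section 3.3.1 describes the data. Blood is taken for liver function, haemoglobin and "estradiol, progesterone, LH, FSH, SHBG, androstendione and DHEAS once a month". Treatment "will be taken orally every other day for 3 months". Urinary cortisol over 24 hours and body composition by BIA are measured at the outset, and "These tests will be repeated after the treatment period". Body composition and cortisol have their own objective in section 3.1.2: "To study the effect of mifepristone on body composition and cortisol levels".

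Two other kinds of outcome get different methods in the same section. For myoma volume a repeated "measures model with the baseline volume as a covariate will be used to" compare the groups over time. For tissue assays, "the paired and unpaired Wilcoxon´s tests will be used as appropriate".

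**The concern.** A two-sample t-test takes one value per woman. With monthly draws over 3 months there are several, and the protocol does not say which is tested or how they are combined. It also does not say that the comparison uses each woman's own starting level. Both sources of information reduce variance, and the volume analysis already uses them.

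Scale is a second, separate matter. Hormone, SHBG, liver-enzyme and cortisol concentrations cannot be negative and may be skewed. Section 3.1.1 says that, given in the follicular phase, "mifepristone inhibits the process of follicular maturation and blocks ovulation", and section 3.3.1 fixes no cycle phase for sampling. Cycle-dependent hormones may therefore be widely spread, and differently so in the two arms. If the t-test is run on untransformed values, a few high results can carry much of the mean.

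With about 20 women per arm, lost precision could be read as absence of an effect on hormones or cortisol.

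**Working it through.** **The plan's own figure.** The only computed sample size is for percentage volume change: SD 10, difference 10, one-sided 5%, 90% power. n per group = 2 × (1.645 + 1.282)² × (10/10)² = 17.1, so 18. With 10% drop-out, 18/0.9 = 20 per group and 40 in total. This reproduces (exact power at 18 is 90.2%) and does not depend on the present point. No such figure is given for laboratory values.

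**Inputs for the check.**
- 18 per arm: from the Protocol.
- Two-sided 5%: assumed, because the one-sided level is stated only for volume.
- Three on-treatment samples: inferred from monthly draws over 3 months.
- A pre-treatment blood value: assumed to be the first monthly draw.
- Correlation ρ between any two of a woman's values, 0.3 to 0.7: assumed.
- Lognormal values with log-SD s: assumed. The documents give no distribution, SD or CV.
- True effect 0.95 log-SD: chosen to give about 79% power with one log value.

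**Repeats and baseline (log scale).** The noncentrality is 0.95 × √(18/2) / √V = 2.85/√V, where V is the variance relative to one value.
- One value: V = 1.
- Mean of three: V = (1 + 2ρ)/3.
- Mean of three, adjusted for baseline: V = (1 + 2ρ)/3 − ρ².
- One post-treatment value, adjusted for baseline (the cortisol case): V = 1 − ρ².

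| ρ | One value | Mean of three: V, power | Mean of three + baseline: V, power | One value + baseline: V, power |
|---|---|---|---|---|
| 0.3 | 79% | 0.533, 97% | 0.443, 98.6% | 0.91, 83% |
| 0.5 | 79% | 0.667, 92% | 0.417, 99.0% | 0.75, 89% |
| 0.7 | 79% | 0.800, 87% | 0.310, 99.9% | 0.51, 97% |

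Two ways of carrying out the t-test on repeated values would also affect false positives. In simulation with ρ from 0.3 to 0.7, a separate test at each of three visits gives an 11-14% chance of at least one false positive. Pooling all samples as if independent gives a type I error of 12-22%. The Protocol states neither practice, and excludes neither.

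**Scale alone (one value per woman).** Simulation with 40,000 trials per setting. CV = √(exp(s²) − 1) and the true ratio is exp(0.95s).

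| s | CV | Ratio | Raw t-test | Log t-test | Loss (points) |
|---|---|---|---|---|---|
| 0.3 | 0.31 | 1.33 | 77.2% | 79.1% | 1.9 |
| 0.5 | 0.53 | 1.61 | 74.8% | 79.5% | 4.7 |
| 0.8 | 0.95 | 2.14 | 66.3% | 78.8% | 12.5 |
| 1.0 | 1.31 | 2.59 | 59.8% | 79.2% | 19.4 |

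The type I error of the raw test is about 5% at s = 0.3 and falls to 3.8% at s = 1.0.

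**Separating the two gains.** Power of a raw-scale t-test on each woman's three-month mean, at ρ = 0.3/0.5/0.7:
- s = 0.3: 96/92/86%
- s = 0.5: 95/90/84%
- s = 1.0: 88/80/72%

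On the log scale it is 97/92/87%, whatever s is. At modest skew almost all of the gain comes from using the repeats. The log scale adds much only when skew is strong.

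**The case against.** The strongest reply is that the Protocol names a test and nothing more. A Student's t-test can be run on logs, on changes or on a per-woman mean, and such details of secondary outcomes are commonly left to a statistical analysis plan, which may exist. The trial calls itself a pilot and is sized only on volume. Most of this stands, and it rules out several stronger readings.

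- A reader might infer that the plan fixes a raw-scale analysis of right-skewed data, so that real effects are missed. The scale is not stated and no distribution is given. Skew is plausible for cycle-dependent hormones but need not hold for every analyte. The simulated lognormal data with a multiplicative effect also favour the log scale, and they do not represent a mixture of cycle phases.
- A reader might infer that the test is invalid. On one value per woman, in the simulated settings, it is not: its type I error is at or below about 5%.
- A reader might extend the argument about monthly repeats to cortisol, the one laboratory measure named in an objective. Cortisol is measured only before and after treatment, so only baseline adjustment and scale apply to it.

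What the reply does not remove is that this section chooses a method for laboratory values. It gives volume a repeated measures model with baseline and gives the monthly laboratory values neither.

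**Conclusion.** The point holds as a free improvement in the analysis of secondary outcomes. Under the stated assumptions, using the repeats raises power from 79% to 87-97%, and adding baseline brings it to about 99%. For cortisol, baseline adjustment alone gives 83-97%. The raw-scale loss is separate and conditional: negligible at log-SD 0.3 and about 19-20 points at 1.0, with nothing in the Protocol to place any analyte in that range. Effects may be missed; the documents do not show that they will be. The planned 40 women and the volume analysis are untouched.

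**What to change.** Replace the t-test wording for laboratory values as follows.
- Monthly hormones, SHBG and liver values: compare the arms with the repeated measures model already planned for volume, with the pre-treatment value as covariate. Alternatively, compare each woman's on-treatment mean adjusted for her pre-treatment value. State that this is one comparison per analyte, not one per visit.
- Urinary cortisol over 24 hours: compare the post-treatment value between arms, adjusted for the pre-treatment value.
- Analyse these concentrations on the log scale and report geometric mean ratios with confidence intervals. Keep haemoglobin and BIA untransformed.
- State that the first blood sample is drawn before treatment, since the adjustment relies on it.

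The cost is analysis wording only. If the first monthly draw is at the start, no visit, sample or patient is added. The one drawback is that results are stated as ratios rather than differences.

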**3.4. Project management**

The project will be conducted at the Stockholm WHO centre for Research in Human Reproduction, Karolinska Hospital.

**3.5. Links with other projects.**

None

**3.6. Main problems anticipated**

The principal investigator has vast experience in ultrasound examination technique and the centre has also a well equipped laboratory for the experimental work concerning the myometrial tissue. Some of these analyses will be perfomed in collaboration with associate professor [name], Dept. of Obstetrics and Gynecology, UAS, Uppsala. The fine-needle aspiration for cytology will be performed and analyzed in a near-by laboratory by skilled physicians. Analyses will be performed in collaboration with [name]

Since 50 mg Mifepristone tablets are not available in Sweden, 200 mg tablets will be divided into 4 pieces containing approximately 50 mg each. An possible uneven active drug content in the 4 pieces will have no practical implication since doses ranging from 12.5 mg of mifepristone has previously been shown to be effective. Doses much higher than 25 mg have been shown not to be harmful. The long half life of mifepristone is probably also of importance to make a every-second-day approach possible. This approach has previously been successfully used in a clinical study.

Mifegyne placebo tablets are not available from Exelgyn. B-vitamin tablets will therefore be used instead of placebo. The B-vitamin tablets will not influence the studied parameters.

**3.7. Expected study outcome**

Results from this study will increase the knowledge on medical alternatives in leiomyomata treatment and also on the antiprogestagen effect on breast proliferation.

**4. Ethical consideration**

Obtaining fine-needle biopsies from the breast has been proved to be a simple and safe procedure. Previous studies have shown that daily treatment with up to 200 mg for a period exceeding 3 months, is safe.

Approval has been obtained from the Karolinska Hospital´s ethical committee

**4.1. Informed consent and confidentiality**

All potential volunteers will be informed about the aims and protocol of the study, expected efficacy of the treatment and the right to withdraw from the study at any time. They will also be informed of the fact that a monitor, not involved in the study will review the data collected. Women participating in the study will be asked to sign a consent form. See appendix (in Swedish)

**4.2. Risk-benefit assessment**

The outcome of this study may give valuable information for the development of non-surgical therapy for women suffering from uterine fibroids. It may also give information on the effect of mifepristone on the breast.

There is no previously described adverse event connected to the proposed procedures.

### Adverse Events

Any unexpected adverse event that occur during the study will be reported to Läkemedelsverket according to LVFS 1996:17. This will also be recorded in the patient file.

The file will be kept for 15 years after end of study.
